**Methods:**

This stage II trial is a Sequential, Multiple Assignment, Randomized Trial (SMART). The hypothesis is that MICT augmented with high-intensity interval training (HIIT) or combined aerobic and resistance exercise (CARE) will improve aerobic fitness, WMHv, and AD/ADRD plasma biomarkers. This trial will enroll 108 dyads (participants and their study partners). Participants (*n* = 108) are randomized using a 2:1 allocation ratio to 3-month MICT or 6-month stretching control. After the initial 3-month intervention period for participants assigned to MICT, aerobic fitness is measured with peak oxygen consumption (VO_2peak_) from a cycle-ergometer exercise testing and the shuttle walk test to identify non-response (< 5% increase). Non-responders are subsequently re-randomized (1:1) to either HIIT or CARE for 3 months. Responders continue MICT. All participants are followed for an additional 6 months post-intervention. Primary outcomes are VO_2peak_ measured at 0, 3, 6, 9, and 12 months and WMHv at 0, 6, and 12 months. Secondary outcomes include memory, physical function, behavioral and psychological symptoms of dementia (BPSD), quality of life (QoL), caregiver burden, and AD plasma biomarkers. This trial has 80% power, assuming 18% and 25% attrition at 6 and 12 months, respectively, to detect changes in aerobic fitness.

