### Objectives {7}

The purpose of this manuscript is to describe the study protocol for FIT-AD SMART, which aims to test the effects and mechanisms of 6-month aerobic exercise that is tailored on aerobic fitness response to MICT in community-dwelling older adults with early symptomatic AD. FIT-AD refers to Function Improvement through aerobic exercise Training in older adults with AD and SMART refers to Sequential, Multiple Assignment, Randomized Trial design. The FIT-AD SMART was built on findings from the FIT-AD Trial that showed individual differences in aerobic fitness responses to MICT to:Aim I. Test the effects of aerobic exercise on aerobic fitness, white matter hyperintensity (WMHv), and patient-centered outcomes in older adults with early symptomatic AD. H1a: Aerobic exercise (MICT, MICT + HIIT, MICT + CARE) will increase aerobic fitness and reduce WMHv over 6 and 12 months more than stretching. H1b: Aerobic exercise will improve patient-centered outcomes over 12 months in comparison to stretching.Aim II. Determine the best exercise to improve aerobic fitness and reduce aerobic fitness non-responses over 6 months in older adults with early symptomatic AD. H2a: MICT + HIIT improves aerobic fitness the most, followed by MICT + CARE, then MICT only, and then stretching. H2b: HIIT reduces the number of MICT non-responders more than CARE.Aim III. Examine the mechanisms of aerobic exercise’s action on memory in early symptomatic AD. H3: Changes in plasma Aβ_42/40_, phospho-tau181 (ptau181), total tau (t-tau), and neurofilament light chain (NfL) mediate memory responses to exercise.

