### Outcomes {12}

Primary outcomes are aerobic fitness measured at 0, 3, 6, 9, and 12 months and WMHv measured at 0, 6, and 12 months. Secondary outcomes (memory, physical function, BPSD, QoL, caregiver burden) and plasma biomarkers (Aβ_42/40_, p-tau181, t-tau, NfL) are assessed at 0, 3, 6, 9, and 12 months. Exploratory outcomes include discrete cognitive domains (attention, working memory, processing speed, executive function, visuospatial ability, language, other MRI and plasma biomarkers, and study partner outcomes).

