## Statistical methods

### Statistical methods for primary and secondary outcomes {20a}

In the preliminary analyses, univariate (e.g., means, SDs, frequencies) and bivariate (e.g., ANOVA/Kruskal–Wallis, chi-square, correlation) statistics and plots will be used first to examine distributions of and associations among study variables; to identify potential multivariate outliers, influential cases, and implausible values; to explore missing-data patterns; and to check for systematic between-group differences at baseline. To further investigate if model assumptions are met, preliminary linear-regression models predicting 6-month outcomes from group assignment will be estimated; results will inform the choice of link function (e.g., natural log), error distribution (e.g., negative binomial), and/or data transformation. The internal consistency of each multi-item composite measure will be evaluated. Analyses and plotting will be conducted in R 4.1, SAS 9.4 (Aims I–II), and Mplus 8.7 (Aim III). Holm’s approach [52] and fixed-sequence testing procedures [52–54] will be used to control for an overall false discovery rate across multiple tests.

To address H1a, we will estimate between-group differences in aerobic fitness or WMHv change from baseline to 6 months and baseline to 12 months using an ANCOVA-type approach, a generalized linear model (GLM) in which the randomized group (e.g., MICT vs. control) predicts aerobic fitness or WMH volume at 6 months (or 12 months), adjusting for baseline aerobic fitness or WMHv and potentially relevant covariates and confounders identified in preliminary analyses. To address H1b, we will estimate GLMs paralleling those used to address H1a, but with memory, QoL, physical function, BPSD, and caregiver burden as outcomes. We will also perform similar analyses for exploratory outcomes (Table 2).

To address H2a, we will estimate contrasts corresponding to a monotonic ordering of the means [55] in which mean aerobic fitness at 6 months is the highest in the MICT + HIIT group, followed by MICT + CARE, then MICT only, and then stretching. Unlike a typical linear trend analysis, this approach does not require that the conditions (groups) represent equally spaced intervals along a quantitative continuum (e.g., min/day aerobic exercise).

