To address H2b, we will estimate a multivariable logistic regression predicting 6-month responses (non-responder vs. responder) from the R2 group assignment (MICT + HIIT vs. MICT + CARE), adjusting for 3-month VO_2peak_.

To address H3, we will first estimate direct effects of condition initially randomized to group (**X**: a dichotomous indicator of MICT vs. control) on each 6- and 12-month outcome (**Y**: memory). Next, we will estimate indirect (mediated) effects of group (**X**) on memory (**Y**) via one or more 6- or 12-month measure(s) of potential mediators (**M**: e.g., plasma Aβ_42/40_) with structural equation path models using approaches described and implemented by Imai et al. [56], VanderWeele [57], and Muthén et al. [58, 59]. Where warranted, we will adjust estimates of indirect effects for covariates and for X × M interaction effects on outcomes. We will conduct sensitivity analyses to evaluate assumptions about these potential confounders [56]. We will also estimate magnitudes of indirect effects [60].

All analyses will follow the intention-to-treat (ITT) approach to provide unbiased tests of treatment effects. The ITT population will be defined as all randomized participants. We will first examine associations between baseline covariates and missingness in outcomes. Along with dropout records, findings will inform model development to generate multiple complete datasets and, where warranted, the construction of analytic models applied to these datasets, under the assumption that data are missing at random. Imputed datasets will be analyzed separately, and the results pooled to yield estimates of model parameters and associated standard errors. Diagnostic analyses and plots will be used to assess the quality of the imputations [61] and the possibility that data may be missing not at random. Sensitivity analyses based on pattern mixture models with varying assumptions regarding effects of potential missing data on outcome values (e.g., shifts in means) will be used to examine robustness of findings based on missing-at-random assumptions.

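### The H3 mediation model specifies no baseline biomarker or memory term and allows same-visit pairs, so if exercise shifts a biomarker, a pre-existing biomarker–memory correlation can be credited as mediation

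*Protocol article*

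**What the plan says.** Objectives {7} words H3 in terms of changes: changes in plasma Aβ42/40, p-tau181, total tau and NfL "mediate memory responses to exercise".

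The H3 paragraph of Statistical methods {20a} first estimates the effect of the initial randomised group "on each 6- and 12-month outcome" (memory), then indirect effects "via one or more 6- or 12-month measure(s) of potential mediators". No change score is mentioned. On covariates it says only: "Where warranted, we will adjust estimates of indirect effects for covariates and for X × M interaction effects on outcomes". Sensitivity analyses on confounding assumptions are also planned. Section {20b} names demographics and APOE genotype as covariates for the main analyses.

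The other hypotheses in {20a} are more specific. H1a adjusts for the baseline value of its outcome, H1b (which includes memory) uses parallel models, and H2b adjusts for 3-month VO2peak.

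Under Outcomes {12}, memory and the plasma biomarkers "are assessed at 0, 3, 6, 9, and 12 months", so baseline values and time-ordered pairs will be available.

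**The concern.** Group is randomised, so the exercise-to-biomarker path is unbiased with or without baseline terms. The biomarker-to-memory path is an observational association inside the trial. In a model of follow-up levels, that path carries whatever correlation the two variables already had before any exercise. If exercise also moves the biomarker, the product of the two paths is reported as an indirect effect, even when the exercise-induced change does nothing to memory. A same-visit pair adds a second problem, because it cannot show that the biomarker moved before memory did.

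Aim III is the trial's mechanistic conclusion. A false claim here would name a plasma biomarker as the route by which exercise acts on memory.

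**Working it through.** **Inputs from the protocol (Sample size {14}):** H3 with 59 exercise and 30 control completers (89 in all) at 6 months; 81 completers at 12 months; r² of at least 0.12 on each link; power of at least 80%; memory pre-post correlation 0.50 (from H1b); α = 0.05, taken as two-sided.

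**Assumptions, not in the protocol:** baseline biomarker–memory correlation ρ from -0.2 to -0.4; biomarker stability s_M from 0.5 to 0.9.

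**Step 1. Reproduce the stated power.** The test is joint significance of both links, by Fisher z, with r = √0.12 = 0.346 and atanh(r) = 0.361.
- X→M, n = 89: 0.361 × √86 = 3.35, power 0.918.
- M→Y given X: 0.361 × √85 = 3.33, power 0.915.
- Joint: 0.918 × 0.915 = 0.84. A noncentral F calculation gives 0.87.
- At n = 81: 0.891 × 0.887 = 0.79 (noncentral F: 0.82).

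The stated figure of at least 80% is reproduced at 6 months.

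**Step 2. Effect of omitting the baseline values.** Take an autoregressive model with no biomarker effect on memory:
- M6 = s_M·M0 + a·X + error
- Y6 = s_Y·Y0 + error
- corr(M0, Y0) = ρ

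The within-group correlation of M6 and Y6 is then s_M × s_Y × ρ, all of it inherited from baseline. The exercise shift for r² = 0.12 at 59 vs 30 is d = 0.346 × √(1/(0.663 × 0.337)) / √0.88 ≈ 0.78. The false-mediation rate is about 0.918 × the power of the M→Y test at the inherited correlation.

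With s_Y = 0.50:

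| ρ | s_M = 0.5 | s_M = 0.8 | s_M = 0.9 |
|---|---|---|---|
| -0.2 | 7% | 11% | 12% |
| -0.3 | 10% | 18% | 22% |
| -0.4 | 14% | 29% | 36% |

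Worked corner (ρ = -0.4, s_M = 0.9): 0.9 × 0.5 × 0.4 = 0.18; atanh(0.18) × √85 = 1.68; power 0.389; × 0.918 = 0.36. Simulation agrees to within about 1 to 2 points, giving an overall range of about 7% to 37%.

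If memory is much more stable (s_Y = s_M = 0.9, ρ = -0.4), the inherited correlation is 0.324, the M→Y power is 0.873, and the rate is 0.918 × 0.873 = 0.80.

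**Step 3. Exercise does not move the biomarker.** The X→M test is then significant only about 5% of the time, so the joint rate cannot exceed about 5%. Simulation gave 0.2% to 4% in the cells checked here, and about 5% at most over a wider range of correlations.

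**Step 4. Add baseline biomarker and baseline memory.** Under the autoregressive model, simulated false mediation is 4% to 6%. Power for a true mediated effect is almost unchanged (0.849 against 0.861 without the terms).

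**Step 5. A less favourable model.** Suppose biomarker and memory are noisy readings of correlated stable traits, with correlation of size 0.3 to 0.5. The unadjusted rate is then 76% to 94%, and the adjusted rate 6% to 62%. A noisy baseline leaves residual confounding, so adjustment helps but need not cure the problem.

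**The case against.** The strongest reply is that silence is not a decision. The article condenses a fuller plan, covariate lists for path models often sit in an SAP, the text allows covariates and plans confounding sensitivity analyses, and nothing excludes baseline values. This stands to the extent that a reader should not infer that the plan rejects baseline adjustment: none is specified, which is different. It does not remove the point. The same section gives a prior-value adjustment for H1a, H1b and H2b, and it describes the H3 mediator as a follow-up measure while the hypothesis concerns change. Conditional, unnamed covariates do not commit to the two that matter, and a sensitivity analysis does not replace adjusting for a confounder already measured.

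Other stronger readings are also unsupported:
- **A baseline correlation alone yields false mediation.** It does not. Exercise must also shift the biomarker (Step 3).
- **False mediation of 60% to 80% is the expected size.** Rates that high need memory far more stable than the plan's 0.50, or the stable-trait model.
- **The plan pairs a 12-month mediator with 6-month memory.** The wording does not exclude this, but the plan never proposes it, and the same wording also permits the sensible 6-to-12-month pair.
- **The biomarkers are wrongly missing from H1b.** The abstract does hypothesise that exercise "will improve aerobic fitness, WMHv, and AD/ADRD plasma biomarkers", and the H1b models run "but with memory, QoL, physical function, BPSD, and caregiver burden as outcomes". But H1b concerns patient-centred outcomes, and the exercise effect on a biomarker is a randomised comparison that is unbiased without baseline terms. It is a separate matter.

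The calculation also leaves out the planned multiplicity control and the demographic and APOE covariates, so the rates are per mediator test at nominal 5%.

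**Conclusion.** The concern holds in a bounded form. The H3 model as described does not match the hypothesis about changes, allows same-visit pairs, and does not commit to the two baseline values most needed on the unrandomised path.

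The false-positive risk is conditional on exercise moving the biomarker. At the plan's own r² = 0.12 and memory correlation of 0.50, it is about 7% to 37% against a nominal 5%. The baseline correlation and biomarker stability behind that range are assumptions. Baseline adjustment returns the rate to about 5% under an autoregressive model and only reduces it under a stable-trait model. The stated H3 power is not in dispute. This should be corrected before analysis; it does not affect the primary comparisons.

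**What to change.** In the H3 paragraph of Statistical methods {20a}:
1. Adjust the exercise-to-biomarker path for the baseline biomarker.
2. Adjust the biomarker-to-memory path and the direct path for baseline biomarker and baseline memory.
3. Name 6-month biomarker to 12-month memory as the lead model, and label same-visit pairs exploratory. Time order alone does not remove the baseline confounding, so items 1 and 2 apply to every pair.
4. Keep the planned confounding sensitivity analysis, because a noisy baseline can leave residual bias.

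The cost is wording only, as every measurement is already scheduled. The downside is that the lead pair rests on about 81 rather than 89 expected complete cases, with joint power of 0.79 to 0.82 instead of 0.84 to 0.87, and the same-visit results lose confirmatory weight.

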### Criteria for discontinuing or modifying allocated interventions {11b}

After 3 months of MICT, aerobic fitness non-response is determined in a three-hierarchical order as (1) < 5% increase in VO_2peak_ if peak cycle-ergometer exercise test with indirect calorimetry is completed at sufficient effort (e.g., respiratory exchange ratio ≥ 1.0 or HR ≥ 85% of the age-predicted max HR). (2) If exercise test is refused (e.g., participant wishes not to wear testing mask), non-response is indicated by < 10% increase in peak aerobic power (peak watts/kg) on the exercise test. (3) For participants who do not complete the exercise test, non-response is indicated by < 36.5-m increase in the distance of shuttle walk test (SWT). Non-responders are re-randomized 1:1 to HIIT or CARE for 3 months, stratefied by baseline age and random permuted blocks of 3 and 6. Responders continue MICT for 3 more months.

HIIT. An evidence-based “Scandinavian-style” HIIT protocol is used [22, 23]. This protocol includes 40 min of HITT comprising 5 sets of 4-min high-intensity cycling followed by 4-min moderate-intensity cycling. After a 10-min warm-up, participants progress to moderate intensity before the first set of HIIT. High intensity is prescribed as 80–85% HRR or RPE 15–16 for the first 8 weeks and increased to 80–90% HRR or RPE 15–17 after week 8. Following the HITT session, a 10-min cool-down period is conducted.

CARE. CARE includes 20-min resistance exercise followed by 30-min cycling. Resistance exercises target six major muscle groups (chest press, shoulder press, squats, rows, leg press, calf raises), are performed on exercise machines, and are adapted for any mobility or musculoskeletal issues reported by participants. Intensity is based on estimated one-repetition maximal strength (1RM) and progress following guidelines for older adults [24]. It starts with 2 sets of 10–12 repetitions at moderate intensity (50–60% 1RM, 9–11 RPE) and progressively increases to 70–85% 1RM or 13–16 RPE by week 7. Rest intervals are 1–2 min between sets. Cycling intensity is 65–75% HRR or RPE 12–14, like exercise prescription used during the MICT.

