### Sample size {14}

Assuming 18% attrition at 6 months and 25% attrition at 12 months, the sample size of 108 participants should result in a population of *n* = 89 at 6 months and *n* = 81 at 12 months. Under H1a, tests comparing participants assigned to MICT vs. control at R1, 89 complete cases (60 intervention [MICT, MICT + HIIT, MICT + CARE]; 29 control) at 6 months should result in 80% power to detect significant between-group differences in VO_2peak_ and WMHv changes, assuming a standardized between-group difference of *d* = 0.65 (based on a clinically meaningful difference in VO_2peak_ of 3.12 mL/kg/min) and SD = 4.8 (derived from previous research [49]), a pre-post correlation (*r*) in VO_2peak_ of 0.50, and *α* = 0.05 [50]; at 12 months, 81 complete cases (54 intervention; 27 control) should result in 80% power to detect differences of *d* ≥ 0.60, assuming pre-post *r* of 0.50 and *α* = 0.05. For models under H1b, 89 complete cases at 6 months should result in 80% power to detect between-group differences in change of *d* ≥ 0.57 for memory, quality of life (QoL), physical function, and behavioral and psychological symptoms of dementia (BPSD) scores, assuming pre-post *r* of 0.50 and *α* = 0.05; at 6 and 12 months, 81 complete cases should afford power to detect differences in change of *d* ≥ 0.60. For H2a, simulations conducted in R with the latest version at the time of data analyses (20,000 replications for each of 7 effect size scenarios) indicate that tests for a monotonic ordering of group means (i.e., MICT + HIIT > MICT + CARE > MICT > stretching) on VO_2peak_ should have power ≥ 80% for orderings comprising small MICT + HIIT vs. MICT + CARE and MICT + HIIT vs. MICT differences (*d*s = 0.25–0.35) and moderate MICT only vs. stretching differences (*d*s = 0.40–0.55). For H2b, assuming *n* = 13 per group, logistic-regression models are 80% powered to detect large between-group (MICT + HIIT vs. MICT + CARE) differences in number of responders (vs. non-responders), e.g., ≤ 2 non-responders in MICT + HIIT vs. ≥ 11 non-responders in MICT + CARE at *α* = 0.05. For H3, potential mediation of exercise effects (**X**: MICT [*n* = 59] vs. control [*n* = 30]) on memory (**Y**s) through AD/ADRD plasma biomarkers (**M**s) is ≥ 80% powered to detect mediated effects comprising modest direct associations (*r*^2^s ≥ 0.12) between groups (at R1) and each putative mediator (X → M link) and between each mediator and memory (M → Y link) [51].

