### Methods in analysis to handle protocol non-adherence and any statistical methods to handle missing data {20c}

Protocol non-adherence will be controlled for during data analysis. The ITT population will be defined as all randomized participants. We will first examine associations between baseline covariates (e.g., group, demographics, baseline outcome values) and missingness in outcomes. Along with detailed study records of reasons for dropout, these findings will inform model development to generate multiple complete datasets and, where warranted, the construction of analytic models applied to these datasets, under the assumption that data are missing at random. Imputed datasets will be analyzed separately, and the results pooled to yield estimates of model parameters and associated standard errors. Diagnostic analyses and plots will be used to assess the quality of the imputations [61] and the possibility that data may be missing not at random. Sensitivity analyses based on pattern mixture models with varying assumptions regarding effects of potential missing data on outcome values (e.g., shifts in means) will be used to examine robustness of findings based on missing-at-random assumptions.

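### The unbiased intention-to-treat claim for all analyses cannot hold for H2a, whose three exercise groups are formed by month-3 response and a second randomisation

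*Protocol article*

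**What the plan says.** In the Protocol article, section {20a} (statistical methods), the last paragraph makes a statement about every analysis: "All analyses will follow the intention-to-treat (ITT) approach to provide unbiased tests of treatment effects". It adds: "The ITT population will be defined as all randomized participants". The same section defines the H2a test as an ordering of four groups: "mean aerobic fitness at 6 months is the highest in the MICT + HIIT group, followed by MICT + CARE, then MICT only, and then stretching".

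Section {11b} says how the exercise groups arise. "After 3 months of MICT, aerobic fitness non-response is determined in a three-hierarchical order", and then: "Non-responders are re-randomized 1:1 to HIIT or CARE for 3 months". Responders stay on MICT. Trial design {8} gives the same structure.

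Sections {20a} and {20c} handle missing data by multiple imputation under missing at random, with pattern-mixture sensitivity analyses. Both speak of missing outcomes. Neither says how a participant without a month-3 response class or a second-stage arm enters an H2a group.

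Sample size {14} begins: "Assuming 18% attrition at 6 months and 25% attrition at 12 months". It gives no figure for month 3.

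**The concern.** ITT needs a group label that every randomised participant carries from randomisation. H1a, H1b and H3 have one, the first-stage arm. H2b is tied explicitly to the second-stage assignment among those re-randomised. H2a has no such anchor: three of its four labels do not exist until a month-3 result is known, and two of those also need a second randomisation.

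A MICT participant who leaves before then must still be handled somehow, and each handling has a consequence:

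- **Coded as MICT only.** A group defined as month-3 responders is diluted with people of unknown response.
- **Left out.** The analysis is no longer of all randomised participants, and early leavers are removed from the exercise side alone.
- **Response class and second-stage arm imputed.** All randomised participants are kept, but the plan does not say this will be done.

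What is at stake is the stated property of the H2a test, and a choice that would otherwise be made late. Section {17a} exempts the statistician from blinding.

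**Working it through.** **1. Group definitions side by side**

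| H2a group | Fixed by | Known for someone lost before month 3? |
|---|---|---|
| Stretching | First randomisation | Yes |
| MICT only | Month-3 response | No |
| MICT + HIIT | Month-3 non-response and second randomisation | No |
| MICT + CARE | Month-3 non-response and second randomisation | No |

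The shuttle-walk fallback in {11b} covers people who attend month 3 without completing the cycle test. It does not cover people who have already left. The contradiction therefore follows from the text alone. The rest of this check concerns its size.

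**2. The plan's own attrition figures**

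108 × 0.82 = 88.6 (stated 89) and 108 × 0.75 = 81 (stated 81). Both reproduce. The 2:1 allocation gives 72 MICT and 36 stretching.

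**3. MICT participants lost before month 3**

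By month 6, 72 × 0.18 = 13.0 are lost. The share falling before month 3 is an assumption.

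| Assumption | Lost before month 3, of 72 |
|---|---|
| None of the 18% | 0 |
| One third | 72 × 0.06 = 4.3 |
| Half (even spread) | 72 × 0.09 = 6.5 |
| Constant hazard | 72 × (1 − √0.82) = 6.8 |
| Two thirds | 72 × 0.12 = 8.6 |
| All of it | 13.0 |

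**4. Shift in the MICT-only mean if they are coded to that group**

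- Responder share: {14} has 60 exercise completers at 6 months for H1a and 13 per second-stage arm for H2b. This implies (60 − 26)/60 = 57%.
- Responders among those remaining: (72 − 6.5) × 0.57 = 37.3.
- Early leavers as a share of the enlarged group: 6.5/(37.3 + 6.5) = 15%.
- Responder mean minus whole-arm mean at 6 months, simulated with SD 4.8 and baseline correlation 0.5 (both from {14}), and an assumed month-3 to month-6 correlation of 0.5 to 0.8 and gains of 0.40 to 0.65 SD: about 0.65 to 2.6 mL/kg/min on a change or baseline-adjusted scale.
- Shift, if imputed leavers sit at the whole-arm mean: 0.15 × 0.65 = 0.10 to 0.15 × 2.6 = 0.39 mL/kg/min. Dividing by 4.8 gives 0.02 to 0.08 SD.
- On raw 6-month means it is smaller, about 0 to 0.15 mL/kg/min.
- At the upper bound of 13 leavers: responders 59 × 0.57 = 33.6, share 13/46.6 = 28%, shift 0.04 to 0.15 SD.

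For scale, {14} plans on small steps of 0.25 to 0.35 SD between the upper groups. The standard error of a contrast of 13 HIIT participants with 37 responders is √(1/13 + 1/37) = 0.32 SD, so the central shift is about 0.06 to 0.25 of one standard error.

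**5. Effect of leaving them out**

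If early leavers gain nothing, dropping 9% of the exercise arm overstates the exercise-versus-stretching effect by 1/0.91, or about 10%. The assumption of no gain is not from the plan.

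**6. No dropout at all**

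An illustrative simulation assumed baseline mean 18 and SD 4.8, mean gain 1.5 with SD 2.5, measurement SD 1, and no added effect of HIIT or CARE. It gave 41% non-responders. The 6-month means were 20.8 in responders and 17.7 in non-responders, from selection alone. The size depends on these inputs. The point is that the ordering mixes treatment with response status whether or not anyone leaves.

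**The case against.** The strongest reply is that this is detail for the analysis plan. The article sets out the framework (all randomised, multiple imputation, sensitivity analyses), and the row an early leaver occupies belongs to the imputation model. Month-3 VO2peak is a scheduled outcome, so a completed dataset could yield a response class, leaving only the second-stage arm to assign. That is fair for the mechanics. It does not rescue the sentence, which asserts for all analyses a property that H2a lacks by its own definition.

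Other parts of the reply stand, and they limit the point:

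- A reader might infer that the plan forces a choice between coding early leavers as MICT only and dropping them. It does not. Nothing in {20a} or {20c} rules out imputing the group, and nothing says the first-stage label will be carried over.
- A reader might infer from {20c}, which lists "baseline covariates (e.g., group, demographics, baseline outcome values" among predictors of missingness, that the four H2a groups are treated as baseline variables. The natural meaning there is the first-stage arm, which is known for everyone.
- A reader might infer that early dropout tilts H2a towards its hypothesis. Coding leavers as MICT only does lower that group's mean, but it offsets only a small part of a responder advantage that itself works against HIIT exceeding MICT. The net direction is not established.

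**Conclusion.** The point holds in a limited form. The claim of an unbiased ITT test in all randomised participants is wrong for H2a, because three of its four groups are defined after randomisation and early MICT leavers belong to none of them. Stretching is defined from the start. H1a, H1b and the first-stage group effect in H3 are unaffected, and H2b compares arms as re-randomised.

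The numerical effect of early leavers is small: about 0.02 to 0.08 SD with 6 to 7 leavers, and at most about 0.15 SD with all 13. This rests on an assumed timing of dropout, a responder share inferred from {14} and assumed correlations between visits. A reading of serious bias from early dropout is not supported. The larger reason that the unbiased claim fails for H2a is the comparison of responders with re-randomised non-responders, which needs no dropout at all.

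**What to change.** In {20a} and {20c}:

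1. Limit the ITT and unbiased statement to the first-stage comparisons (H1a, H1b and the first-stage group effect in H3) and, for H2b, to participants as re-randomised at the second stage.
2. For H2a, state that month-3 response class and, for imputed non-responders, the second-stage arm (1:1) are imputed jointly with VO2peak. Early leavers are then spread over the three exercise groups in each dataset and are never coded MICT only by default.
3. Describe the H2a ordering as a comparison of groups partly defined by post-randomisation response, not as an unbiased ITT test.

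Step 2 alone is not enough, because it leaves the responder selection untouched. Requiring 3-month retention in stretching as well would not restore an unbiased comparison either.

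The cost is one extra imputation step, slightly wider H2a intervals and a weaker stated claim for H2a. Recruitment is planned to run to March 2027, so the change can still be pre-specified.
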